## Abstract

**Background:**

Skin cancer, including basal cell carcinoma (BCC), has become a major health care problem. The limitations of a punch biopsy (at present the gold standard) as diagnostic method together with the increasing incidence of skin cancer point out the need for more accurate, cost-effective, and patient friendly diagnostic tools. In vivo reflectance confocal microscopy (RCM) is a noninvasive imaging technique that has great potential for skin cancer diagnosis.

**Objective:**

To investigate whether in vivo RCM can correctly identify the subtype of BCC and to determine the cost-effectiveness of RCM compared with punch biopsy (usual care). Study design: Randomized controlled multicenter trial.

**Methods:**

On the basis of 80% power and an alpha of 0.05, 329 patients with lesions clinically suspicious for BCC will be included in this study. Patients will be randomized for RCM or for a punch biopsy (usual care). When a BCC is diagnosed, surgical excision will follow and a follow-up visit will be planned 3 months later. Several questionnaires will be filled in (EQ-5D, EQ-5D VAS, iMTA PCQ, and TSQM-9). We will perform statistical analysis, cost-effectiveness, and patient outcome analysis after data collection.

**Results:**

This research started in January 2016 and is ethically approved. We expect to finish this study at the end of 2018.

**Conclusions:**

In this study, we will investigate whether RCM is at least as good in identifying BCC subtypes as conventional pathological investigation of skin biopsies. Anticipating that RCM is found to be a cost-effective alternative, it saves on direct medical consumption like labor of the pathologist and other medical personnel as well as materials related to treatment failure with at least equal effectiveness.

**Trial Registration:**

Clinicaltrials.gov NCT02623101; https://clinicaltrials.gov/ct2/show/NCT02623101 (Archived by WebCite at http://www.webcitation.org/6id54WQa2)

## Introduction

### Skin Cancer

Skin cancer is a common type of cancer and its incidence is increasing rapidly in Western countries [1-3]. This cancer comprises two types: melanoma (MM) and nonmelanoma skin cancer (NMSC). NMSC is further divided into basal cell carcinoma (BCC), squamous cell carcinoma (SCC), and its precursors actinic keratosis (AK) and Bowen disease. In the Netherlands, the registry of NMSC is poor. However, based on recent literature and guidelines, it is estimated that the incidence of malignant skin tumors and the premalignant AK is around 235,000 in 2015. This will have a major impact on our health care system. Moreover, it is predicted that numbers will rise at the rate of 4.5-8% per year, depending on the type of skin cancer. Currently, in case of suspicion of NMSC, the pathological examination of a punch biopsy is the gold standard, according to the Dutch guidelines. In case of clinical suspicion of AK, the diagnosis is made *à vue*, without pathological confirmation. Already in 2003 in the United States, skin cancer was found to be among the most costly of all cancers to treat. Therefore, it is evident that skin cancer places an enormous burden on health care systems with increasing costs [4]. In case of suspicion of skin cancer, it is important to diagnose and treat it in an early phase, preferably in a patient friendly manner. As BCC is the most common skin cancer (about 75% of all skin cancers), this study will focus on studying this skin cancer type. Clinically, BCC can vary in appearance but is often characterized by small, translucent, or pearly papules, with telangiectasias [5]. In the past, the diagnosis was mainly made clinically. However, noninvasive therapies have become available; therefore, determination of the BCC subtype has become more important. For this reason, pathological analysis of a punch biopsy is currently the gold standard to confirm the clinical diagnosis and determine the subtype of BCC. The following subtypes of BCC can be distinguished: superficial (sBCC), nodular (nBCC), aggressive BCC (micronodular (mnBCC), and infiltrative (iBCC)) [6]. It is experienced that there is a sample error in 29% of the cases with the conventional diagnostic procedure, resulting in an incorrect subtype diagnosis [7]. For this reason and because of the increasing incidence of skin cancer, more accurate, cost-efficient, and patient friendly diagnostic tools are desirable.

### Reflectance Confocal Microscopy

Reflectance confocal microscopy (RCM) is a noninvasive imaging technique. It provides real-time images of cell and tissue structures and in vivo dynamics, without the need for ex vivo tissue samples. RCM visualizes human skin up to a depth of around 250 μm [8-12]. Refractive index differences between cells and surrounding tissue provide the contrast. The contrast of RCM imaging of the skin is mainly provided by melanin and keratin [10]. Most, but not all, tumors can be visualized. For thicker tumors, RCM may help to find the optimal localization to perform a punch biopsy, as superficial features in these tumors may help to spot these lesions [13]. Moreover, RCM can image the whole tumor. RCM features for NMSC have been described that showed a high correlation with conventional pathological features [13-15]. These features allow diagnosing AK, SCC, and BCC [13-15]. For both the BCC subtypes, nodular and micronodular BCC, the following RCM characteristics are described: tumor nests with peripheral palisading, branch-like structures, fibrotic septa, and increase of vascular diameter. The size and shape of the tumor nests allows further distinction between these BCCs. Solar elastosis and tumor nests connected with the basal cell layer characterize superficial BCC [14]. iBCCs are more challenging to visualize due to their histological complex appearance and deeper location [16].

Only few studies report data about diagnostic accuracy of RCM for primary BCC diagnosis [14,16-19]. These studies show a high sensitivity and specificity for RCM as diagnostic tool for BCC. Although these show the potential of RCM in BCC diagnosis, prospective large-scale studies are lacking. In addition to BCC diagnosis by RCM in general, no diagnostic accuracy data were reported on determination of BCC subtype by RCM. Such studies are required for implementation of RCM in the routine patient care and incorporation into the health insurance system. Implementation of RCM in the routine patient care settings has the advantage of making a diagnosis at the first consultation and therefore, the patient can be treated at short term. A second consultation for explaining the diagnosis and performing the treatment might be unnecessary. Therefore, time saved by using the RCM can be used for other new patients.

### Objectives

The primary objective of this study is to investigate whether in vivo RCM can identify the subtype of BCC at least as correctly as a skin punch biopsy. We are hypothesizing that RCM imaging allows correct identification of the BCC subtype (nBCC, mnBCC, sBCC, iBCC, and mixed type BCC), and true and false positive results are equal or better as compared with conventional pathological investigation of skin biopsies (gold standard). It is postulated that RCM is more cost-effective and patient friendly compared with the current procedure. Therefore, the quality of life (Qol), costs, and quality adjusted life years (QALYs) will be evaluated as the secondary outcome measures. Overall, with the implementation of RCM in dermatology skin cancer care, it is aimed to contribute to cost-effective, noninvasive, patient friendly diagnostics.

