### Power Calculation

The primary outcome in this study is the percentage of correctly identified subtype of confirmed BCC after excision (gold standard in this study). We assume that this is 71% when a punch biopsy is used and 85% when RCM is used (based on an ongoing study). In this case, 148 patients are needed per group to obtain a power of 80% (Fisher’s-exact, two-sided, alpha=0.05). We expect that 10% of the patients with a clinically suspected BCC will not have histopathologically confirmed BCC. Therefore, we will include approximately 329 patients with a clinical suspicion of BCC. In this multicenter randomized controlled trial (RCT), it is also possible to obtain empirical estimates of the (cost-) effectiveness in daily clinical practice, beyond the diagnostic value. The expected benefit of the experimental diagnostic tool is anticipated at €92 per patient. On the basis of a conservative choice of the SD of €100 and the CI of 95%, 146 patients per group are required. Counting a 10% possible dropouts, around 322 patients need to be included.

To answer both questions, in total 329 patients suspected with a clinical suspected BCC will be included in this study.

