### Analysis

After data collection, analyses will be performed. The Fisher’s-exacts test will be used to test the differences in the primary outcome between the two study arms (biopsy, RCM) for statistical significance. Multivariable logistic regression will be used to study possible differences between the subtypes and the effect of possible other variables. This will be done in order to evaluate variables or sets of variables for its discriminative character that can be used to make protocols and guidelines for future Dutch RCM users.

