### Patient Outcome Analysis

The effect analysis adheres to the design of a superiority/equivalent RCT and measures diagnostic performance and Qol at baseline, and at fixed points along the follow-up of the RCT. To measure the quality of the health status of the patients, a validated so-called health-related quality of life (HRQoL) instrument will be used, the EuroQol-5D-3L (EQ-5D) [23]. This HRQoL instrument will be completed by the patients and is available in a validated Dutch translation [24]. The EQ-5D is a generic HRQoL instrument comprising five domains: mobility, self-care, usual activities, pain/discomfort, and anxiety/depression. The EQ-5D index is obtained by applying predetermined weights to the five domains. This index gives a societal-based global quantification of the patient’s health status on a scale ranging from 0 (death) to 1 (perfect health). Patients will also be asked to rate their overall HRQoL on a visual analogue scale (EQ-5D VAS) consisting of a line ranging from 0 (worst imaginable health status) to 100 (best imaginable). The patient outcome analysis will be complemented with a CVM questionnaire and measures of satisfaction and pain related to diagnosing subtype BCC.

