## Discussion

Considering the increasing skin cancer problem, including BCC, and the disadvantages of the current diagnostic gold standard, histopathological diagnosis of a punch biopsy, indicates the need for cost- and time-efficient diagnostic tools with high accuracy for diagnosing skin cancers. These tools should be able to distinguish between skin cancer types and should be able to determine the correct BCC subtype, as different subtypes of BCCs are treated differently. Biopsies often result in sampling errors, as only a small part of the tumor is investigated resulting in potentially inappropriate chosen therapies. As a sample error may lead to treatment failures or recurrences, other subsequent treatments are needed. This will eventually lead to increasing costs. In addition, the conventional method is unfriendly for patients, as it is invasive, painful, and might result in scarring. Furthermore, the diagnosis cannot be made instantly.

To contribute to implementation of RCM as noninvasive skin cancer diagnostic tool, this study will investigate whether RCM is at least as good in identifying BCC subtypes as conventional histopathological investigation of skin biopsies. Hypothesizing that RCM is a cost-effective alternative to the present care, it saves on direct medical consumption like labor of the pathologist and other medical personnel as well as materials related to treatment failure with at least equal effectiveness.

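### The objective asks whether RCM is at least as good as biopsy, but the sizing and primary test are for superiority, so a non-significant result would leave that question unanswered

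*Protocol article*

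**What the plan says.** The aim is framed in one direction. The Objectives section asks "whether in vivo RCM can identify the subtype of BCC at least as correctly as a skin punch biopsy" and hypothesises that "true and false positive results are equal or better as compared with conventional pathological investigation of skin biopsies". The Discussion repeats that "this study will investigate whether RCM is at least as good in identifying BCC subtypes as conventional histopathological investigation of skin biopsies", and the abstract's Conclusions say the same.

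The Patient Outcome Analysis section labels the design differently: "The effect analysis adheres to the design of a superiority/equivalent RCT".

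The operative statistics are those of a superiority trial. On the primary outcome, the percentage of correctly subtyped BCC, the Power Calculation section says: "We assume that this is 71% when a punch biopsy is used and 85% when RCM is used". On that basis "148 patients are needed per group to obtain a power of 80"%, with a two-sided Fisher's exact test at alpha 0.05. In the Analysis section, Fisher's exact "test will be used to test the differences in the primary outcome between the two study arms (biopsy, RCM) for statistical significance". The logistic regression that follows there concerns subtypes and other variables, not this comparison.

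The article gives no non-inferiority or equivalence margin and no rule for concluding that RCM is at least as good.

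**The concern.** A test of no difference can show that RCM is better or that it is worse. When it shows neither, it does not establish that RCM is no worse than biopsy by some tolerable amount. That needs a margin and a confidence limit compared with it. The objective counts equal accuracy as success, yet the planned test has no outcome that confirms equality.

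This matters beyond the primary endpoint. The abstract's Conclusions and the Discussion rest the expected savings on effectiveness at least equal to that of biopsy. If the Fisher test is non-significant, that premise is untested, and a margin chosen after the results are known would carry little weight.

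**Working it through.** **Inputs (Power Calculation section).** Biopsy 71% correct, RCM 85%, 148 per group, two-sided alpha 0.05, Fisher's exact test, 10% of patients without confirmed BCC, 329 in total. True RCM rates other than 85%, and all margins, are assumptions used to show the range.

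**Step 1: reproduce the plan's figure.** Exact power is the sum, over all pairs of counts (x, y), of Bin(x; 148, 0.71) × Bin(y; 148, 0.85) for the pairs where the two-sided Fisher p is at most 0.05. The result is 80.1% at 148 per arm and 79.8% at 147. Inflation: 2 × 148 / 0.90 = 328.9, so 329. The arithmetic is right, and it is the arithmetic of a superiority trial.

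**Step 2: what the planned test can conclude.** Same calculation, 148 analysed per arm, biopsy at 71%:

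| True RCM rate | Non-significant | Significantly better | Significantly worse |
|---|---|---|---|
| 85% | 19.9% | 80.1% | <0.1% |
| 80% | 61.2% | 38.8% | <0.1% |
| 71% (equal) | 96.3% | 1.9% | 1.9% |
| 66% (5 points worse) | 87.4% | 0.1% | 12.5% |
| 61% (10 points worse) | 60.3% | <0.1% | 39.7% |

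A non-significant result is the usual outcome when RCM is equal, and also when it is 5 or 10 points worse. It therefore does not separate these cases.

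**Step 3: what a margin would give at 148 per arm.** Power is Φ[(M + p_RCM − p_biopsy)/SE − 1.96], with SE = √[p_biopsy(1 − p_biopsy)/148 + p_RCM(1 − p_RCM)/148], one-sided 2.5%.

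- Both rates 71%: SE = √(2 × 0.2059/148) = 0.0527. With M = 10 points, Φ(0.10/0.0527 − 1.96) = 47%. With M = 5 points, 16%.
- RCM 80%: SE = √[(0.2059 + 0.1600)/148] = 0.0497. With M = 10 points, Φ(0.19/0.0497 − 1.96) = 97%. With M = 5 points, 80%.
- RCM 85%: SE = √[(0.2059 + 0.1275)/148] = 0.0475. With M = 10 points, Φ(0.24/0.0475 − 1.96) = 99.9%. With M = 5 points, 98%.

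For 80% power when both rates are 71%, the number needed per arm is 324 (M = 10) or 1,293 (M = 5). After dividing by 0.90, the totals are 2 × 324/0.90 = 720 and 2 × 1,293/0.90 = 2,874, against the planned 329.

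**The case against.** The best defence is that the sizing and the primary test agree exactly, so this is a coherent superiority trial described in loose prose. Significant superiority also establishes that RCM is at least as good, so under the plan's own assumptions the stated question is answered in 80% of trials. Both points stand. They limit the problem to the non-significant case and make rewording the smallest adequate fix.

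A reader might infer that the investigators intend to read a non-significant result as success, which would leave the error rate of that claim uncontrolled. The article does not say so. Taken as written, non-significance yields no claim and the two-sided 5% level holds. The wording invites the misreading and nothing rules it out, but it remains a risk and not a stated rule. The 87% and 60% figures show how little a non-significant result would exclude. They are not error rates of a declared procedure, and they assume a true RCM rate well below the plan's 85%.

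It may also be said that a confidence interval and an interpretation rule belong in the full protocol or analysis plan, which are not shown. Their absence alone would indeed be no finding. But the objective, design label, sizing basis and primary test are all stated in the article, and they disagree with each other. A margin found elsewhere would not make the published sizing a non-inferiority sizing.

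**Conclusion.** The mismatch is real and should be fixed. It is a contradiction among statements the article itself makes. The planned test answers the stated question only when RCM is significantly better. Otherwise, which is 20% of trials at 85% against 71%, 61% at 80% against 71% and 96% at equal rates, no at-least-as-good claim is supported.

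These figures assume 148 analysed patients per arm, a biopsy rate of 71% and a two-sided Fisher test. The two-sidedness is stated with the sample size and not repeated in the Analysis section.

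Two stronger readings are not supported. The sample size is not wrong, because it reproduces for superiority. Nor can a non-inferiority rule be called free of consequence for patient numbers: 148 per arm is ample if RCM is truly 85%, but weak if the rates are equal and the margin is 5 or 10 points. Randomisation, endpoint and data collection are unaffected.

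**What to change.** Choose one design before outcome data are seen, and make the abstract, Objectives, Analysis, Patient Outcome Analysis and Discussion agree with it.

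**(a) Superiority only.** Restate the objective as whether RCM is better than biopsy. Remove the at-least-as-good wording and the combined design label. State that a non-significant result is not evidence of equivalence. This costs wording only, and the planned size and test stand.

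**(b) Non-inferiority, then superiority.** Fix and justify a margin M. Report the difference in percentage correct (RCM minus biopsy) with a two-sided 95% confidence interval. Claim at least as good only if the lower limit is above −M, then superiority if it is above 0. The fixed order needs no alpha adjustment. State the power of 148 per arm for the chosen M.

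Option (b) requires the sponsor to commit to a margin, which the article does not supply. With illustrative margins of 5 or 10 points, power is 98% or 99.9% at 85% against 71%, but only 16% or 47% if both rates are 71%. The sponsor would have to accept that or enlarge the trial.

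Under (b), also say whether the interval or Fisher's test decides superiority, because the two can disagree near the boundary. For 105/148 against 88/148, Fisher's p is 0.0506 while the Wald 95% interval for the difference, −22.3 to −0.7 points, excludes zero.

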## Methods

### Recruitment, Inclusion, and Study Design

Patients with lesions clinically suspicious (diagnosis *à vue*) for BCC, eligible for RCM, visiting the dermatological departments of the Radboud University Medical Center, Nijmegen, the Canisius Wilhelmina Hospital, Nijmegen, and the Rijnstate Hospital Arnhem-Velp, in The Netherlands will be asked to join this study.

In order to be eligible for participation in this study, a subject must meet all of the following criteria:

Patients must be 18 years and above.Patients must be able to adhere to all requirements of the study.Patients must be willing to give written informed consent.There must be clinical diagnosis/clinical suspicion of basal cell carcinoma.

A potential subject who meets any of the following criteria will be excluded from participation in this study:

A patient participating in other investigational research currently or in the previous 28 days before the studyPatient having a medical condition which excludes participating the research, according to the investigatorIncapacitated subjectsSubjects with lesion(s) on parts of the body which do not allow adequate imaging of the tumor with RCM

When a patient meets these criteria and gives informed consent, he or she is assigned to a randomization arm according to a computer-generated block randomization (Castor) (Figure 1).

**Figure 1 figure1:**
[figure not shown]
Scheme of randomization. Two randomization arms are designed. After inclusion, a patient with a clinical diagnosis of BCC (diagnosis à vue) will be randomized over the two arms. One arm contains the standard procedure of a biopsypunch biopsy, the other arm contains the diagnostic tool to be investigated: RCM. A punch biopsy will also be obtained when there is no suspicion of a BCC using RCM.

### Power Calculation

The primary outcome in this study is the percentage of correctly identified subtype of confirmed BCC after excision (gold standard in this study). We assume that this is 71% when a punch biopsy is used and 85% when RCM is used (based on an ongoing study). In this case, 148 patients are needed per group to obtain a power of 80% (Fisher’s-exact, two-sided, alpha=0.05). We expect that 10% of the patients with a clinically suspected BCC will not have histopathologically confirmed BCC. Therefore, we will include approximately 329 patients with a clinical suspicion of BCC. In this multicenter randomized controlled trial (RCT), it is also possible to obtain empirical estimates of the (cost-) effectiveness in daily clinical practice, beyond the diagnostic value. The expected benefit of the experimental diagnostic tool is anticipated at €92 per patient. On the basis of a conservative choice of the SD of €100 and the CI of 95%, 146 patients per group are required. Counting a 10% possible dropouts, around 322 patients need to be included.

To answer both questions, in total 329 patients suspected with a clinical suspected BCC will be included in this study.

### Outcome Measures

The primary outcome measure is defined as correct subtyping of the BCC after excision. The histopathological diagnosis of the excision specimen will be compared with either the diagnosis made by RCM or a punch biopsy. Secondary outcome measures are Qol, Cost, and QALYs.

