### Procedure

Patients will be assigned to either the RCM or the punch biopsy study arm (Figure 1). When a BCC is diagnosed using RCM or the gold standard (punch biopsy), surgical excision will follow according to standard care-time schedule at the center where the BCC is diagnosed with margins according to the guidelines (3 mm for sBCC and nBCC, 5 mm for aggressive BCC). In case of a BCC, a follow-up visit will be planned 3 months after surgery. If the diagnosis reveals the absence of a BCC, the patients will again be followed-up after 3 months. During visit 1 (diagnostic procedure) several questionnaires will be filled in (EQ-5D, EQ-5d VAS, iMTA PCQ, and TSQM-9). At the follow-up visit after treatment, the questions about satisfaction of the diagnostic procedure will be asked again. In order to establish the added monetary value of RCM, a contingent valuation method (CVM) was used. Patients that belong to the RCM arm and also had a punch biopsy, in which both diagnosis had the absence of a BCC, were interviewed according to the CVM.

RCM will be performed with the commercially available Vivascope 1500 (Caliber imaging & diagnostics, Rochester, NY, USA) according to a standardized protocol. Vivablocks of 4 × 4 mm will be made at the level of the stratum corneum, stratum spinosum, dermal epidermal junction, and dermis in order to find RCM features for BCC and the subtype. Vivastacks will be made in the areas of interest. Movies will be made to document vascularization. When indicated, the Vivascope 3000 handheld device will be used. The RCM user is working for 4 years with the device. If a punch biopsy needs to be obtained according to the randomization scheme, this will occur after local anesthesia (1% xylocaine/adrenaline) and the punch biopsy will have a diameter of 3 mm. The punch biopsy will be taken from the most clinically suspected area of the lesion.

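### The excision specimen is the sole reference, but in the biopsy arm the punch has already removed tumour from it; the scoring rule should cover this, as the bias favours RCM

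*Protocol article*

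**What the plan says.** The outcome is defined in two places in the protocol article. Power Calculation sets the denominator: "The primary outcome in this study is the percentage of correctly identified subtype of confirmed BCC after excision (gold standard in this study"). Outcome Measures sets the reference: "The histopathological diagnosis of the excision specimen will be compared with either the diagnosis made by RCM or a punch biopsy".

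Procedure describes the index test in the biopsy arm: "the punch biopsy will have a diameter of 3 mm. The punch biopsy will be taken from the most clinically suspected area of the lesion". Excision comes afterwards: "When a BCC is diagnosed using RCM or the gold standard (punch biopsy), surgical excision will follow according to standard care-time schedule".

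RCM removes no tissue. The section on reflectance confocal microscopy says of it: "It provides real-time images of cell and tissue structures and in vivo dynamics, without the need for ex vivo tissue samples". The legend of Figure 1 adds one exception in the RCM arm: "A punch biopsy will also be obtained when there is no suspicion of a BCC using RCM".

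Objectives lists mixed type as a BCC subtype in its own right. Nothing in the article combines punch and excision tissue into one reference or says how an excision without residual tumour is scored. The eligibility criteria set no minimum lesion size.

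**The concern.** A reference standard should mean the same thing in both arms. Here it does not. When RCM diagnoses a BCC, the pathologist receives the whole tumour. When a punch diagnoses it, the pathologist receives the tumour less a core from its most suspect part. Randomisation gives no protection, because the difference arises after allocation and through the index test itself.

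Two kinds of biopsy-arm patient are affected.

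- **Complete removal.** The punch contains the entire BCC, so its subtype is that of the tumour. The excision shows no BCC. Under the written rule the patient either is not a BCC confirmed at excision and leaves the analysis, or is scored as a mismatch.
- **Mixed tumour.** The punch contains both components and is correctly read as mixed. The residual holds only one component, so the correct reading is scored wrong.

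Neither can happen to a patient subtyped by RCM. At stake is a superiority claim helped by the scoring rule. The objective that RCM be no worse than biopsy is also exposed, because a slightly inferior RCM could look equal.

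**Working it through.** **Inputs from the article (Power Calculation):** 71% correct with punch, 85% with RCM, two-sided Fisher's exact test at 0.05, 148 per group, 10% without confirmed BCC, 329 in total.

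**The plan's own figure.** Full enumeration of Fisher's test at 71% v 85% gives power 0.798 with 147 per group and 0.801 with 148. Then 2 × 148 / 0.90 = 328.9, that is 329. The sample size reproduces; the weakness is in the outcome rule.

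**Direction.** Whole tumour = punch + residual. Assume both specimens are read accurately.

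- A component the punch missed must lie in the residual, so a punch that is wrong for the whole tumour is also wrong for the residual.
- A component present only in the punch is absent from the residual, so a punch that is right for the whole tumour can be wrong for the residual.

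Scoring against the residual alone can therefore only lower the biopsy result.

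**Size if fully removed tumours are dropped.** Let g be the share of biopsy-arm BCCs removed completely by the punch. The article gives no value, so g is an assumption. These punches are all correct, so the observed biopsy rate is (0.71 − g)/(1 − g) on 148(1 − g) patients. RCM stays at a true 71% on 148.

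| g | biopsy n | biopsy rate observed | chance RCM falsely declared better |
|---|---|---|---|
| 0 | 148 | 71.0% | 1.9% |
| 2% | 145 | 70.4% | 2.6% |
| 5% | 141 | 69.5% | 4.2% |
| 10% | 133 | 67.8% | 7.5% |
| 20% | 118 | 63.8% | 22% |

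**Size if correct punches are scored wrong.** Let f be the share of correct punches scored wrong, by either route; it too is assumed. The observed rate is 0.71(1 − f) on 148 patients: 69.6% at f = 2%, 67.4% at 5%, 63.9% at 10%. The chance of falsely declaring RCM better is 3.5%, 7.8% and 22.0%. Scoring these patients wrong therefore costs the biopsy arm more than dropping the same share.

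**What geometry says.** A 3 mm core takes (3/d)² of the surface of a round lesion of diameter d mm: 100% at 3 mm, 56% at 4 mm, 25% at 6 mm, 9% at 10 mm. On this simple picture only lesions of about 3 mm or less are removed completely. Larger ones can be affected only through the mixed-type route.

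**The case against.** **The scoring of a tumour-free excision is a detail for the full protocol.** The article does not say outright that such a patient is excluded. The allowance of 10% speaks of histopathological confirmation, which a punch could supply. This has some force. But the outcome sentence restricts the denominator to BCC confirmed after excision, and Outcome Measures names the excision as the comparator. A site that follows those two sentences drops the patient or scores a mismatch. That is a stated rule with a consequence, and more than an omission.

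**The mixed-tumour argument can be overstated.** A reader might infer that the punch is treated unfairly whenever it shows one component of a mixed tumour and the residual shows the other. The article does not support that. Mixed type is a separate subtype under Objectives, so a punch showing a single component is wrong against the whole tumour too. That is the sampling error described in the Introduction, and it is no part of this bias.

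**The size is assumed.** This stands. There is no lesion size and no rate of tumour-free excision, and the 22% figure needs a fifth of biopsy-arm BCCs to be removed completely. The planning rate of 71% may also already include some of the effect, if the 29% error behind it came from comparing punch with excision. That would protect the power calculation but would not make the comparison fair.

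**Patients in the RCM arm are punched too.** True, when RCM shows no suspicion of BCC, so the altered reference is not confined to the biopsy arm. These patients have no RCM subtype to be spoiled. Losing such a patient through complete removal would discard an RCM miss, which again favours RCM.

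**A joint reading puts the punch into its own reference.** Also true. A misread punch with a tumour-free excision would count as correct. This is why the joint reading belongs among the sensitivity analyses, with the opposite scoring beside it.

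**Conclusion.** The point holds. With excision as the sole reference, a correct punch can be dropped or scored wrong, while a correct RCM call on a tumour excised intact cannot. The bias runs in one direction, towards RCM, provided both specimens are read accurately.

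Its size cannot be established from the article. With both tests truly 71% correct, losing 2% to 10% of biopsy-arm BCCs moves the false-superiority rate from 1.9% to between 2.6% and 7.5%; at 20% it is 22%. These shares are assumptions, and nothing in the article shows that the larger ones are likely.

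A reader might go further and infer that a positive result would be an artefact, or that the design is unsound. The documents do not support this: the affected share is unknown, it may be small, and one common reference for both tests is a defensible choice. This is a should-fix item and a cheap improvement.

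**What to change.** Amend the outcome definition before the data are analysed.

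1. Keep every punch-proven BCC with a tumour-free excision in the primary denominator of the biopsy arm, and state in advance which scoring is primary.
2. Report the number of tumour-free excisions per arm.
3. Prespecify sensitivity analyses that (a) score these patients correct, (b) score them incorrect, (c) exclude them, which is the excision-only reference, and (d) take existing punch and excision slides, read together, as the biopsy-arm reference under the subtype rule used for RCM-arm excisions. Analysis (d) also covers punches read as mixed with a single-type residual.
4. Claim superiority or equivalence of RCM only if the conclusion holds across these analyses.

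The cost is some wording, some extra slide reading and a few extra analyses. No patient procedure changes. The joint reading tilts towards biopsy because the punch contributes to its own reference; for a claim in favour of RCM that is conservative.
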